### Patient involvement

Patients were involved in the design and are currently involved in the conduct of this research. During the planning stage, priority of the research question, choice of outcome measures and methods of recruitment were informed by discussions with patients through a focus group session and two structured interviews. Patients form the membership of the independent TSC and of the trial management group. Once the trial has been published, participants will be informed of the results in a study newsletter suitable for a non-specialist audience.

### Data collection and management

Trial data collected at each centre by the research podiatrists and clinical research nurses will be recorded on trial-specific CRFs and will be considered the source data. The data manager will review the data being sent at regular intervals and report back to each centre if there is any discrepancy. The original completed CRF will be checked for completeness to ensure there are no missing items. Data will be entered into the database via a bespoke web-based data entry system encrypted using secure sockets layer (SSL).

### Sample size

As this is a feasibility trial the sample size is pragmatic and a power calculation is neither relevant nor possible. In this feasibility trial, while centres are likely to start recruitment in a staggered fashion, our overall target recruitment will be 2 per month per centre up to a total of 76 participants (38 per group). A CI approach has been used to establish feasible adherence rates. Based on an estimated completion rate of 75%, at least 75 patients are required. This is based on obtaining a 95% CI for a single proportion with a specified lower bound of the CI of 0.70 and a marginal error of 0.05. Data collected on proposed secondary outcomes will provide data on which sample size calculations can be performed in the future RCT.

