#### Proposed primary outcome analysis

Analyses will summarise the feasibility outcomes: data from screening, recruitment and follow-up logs will be used to generate realistic estimates of eligibility, recruitment, consent and follow-up rates in the trial population. In addition, adherence data (eg, session attendance and insole/footwear adherence) will be used to contribute to the evaluation of the acceptability and concordance to the insole intervention. Completion rates will be estimated for each of the patient-reported and clinical outcome measures at each time point. All such estimates will be accompanied by appropriate CIs, to allow assumptions to be made in the planning of the definitive trial. The baseline characteristics of individuals lost to follow-up will be compared with those who complete the feasibility trial to identify any potential bias. Means and SDs arising from differences between the intervention and control arms to inform a power calculation for sample size estimate for the main RCT will be made.

Progression to a full trial will occur if the following minimum success criteria are achieved, or if there is reason to believe that suitable enhancements can be made to the full trial to ensure that any concerns are circumvented:70% recruitment of the intended 76 participants within the 13-month recruitment window.75% retention of participants within the 12-month trial period.80% completion rate of primary and secondary outcome measures at baseline, 3 months, 6 months and 12 months.

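### The sample-size statement claims a 95% CI of ±0.05 (lower bound 0.70) from 75 patients; 75 patients give about ±0.10 (lower limit 0.65)

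*Protocol article*

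**What the plan says.** The Sample size section of the protocol article first calls the size pragmatic and says that "a power calculation is neither relevant nor possible". It then gives a precision argument: "A CI approach has been used to establish feasible adherence rates". The result is stated as follows: "Based on an estimated completion rate of 75%, at least 75 patients are required". The basis given is a "95% CI for a single proportion with a specified lower bound of the CI of 0.70 and a marginal error of 0.05". The recruitment target is 76, 38 per group.

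Two progression criteria in the section Proposed primary outcome analysis bear on this: "75% retention of participants within the 12-month trial period" and "70% recruitment of the intended 76 participants within the 13-month recruitment window". The same section says the feasibility estimates will be reported with confidence intervals so that the definitive trial can be planned from them.

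**The concern.** The paragraph fixes every input of a single-proportion precision calculation: the anticipated rate, the confidence level, the margin, the lower bound and the resulting number. For a rate of 0.75, a margin of 0.05 and a lower bound of 0.70 are the same requirement (0.75 − 0.05 = 0.70), so a misprint in one of them would not explain a discrepancy. Seventy-five patients looks far too few for ±0.05 at 95% confidence.

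Precision is what a feasibility trial offers in place of power. A reader of this paragraph, including the steering committee, would expect an observed 75% to support a true rate of at least 70%. If the real interval is twice as wide, that expectation is wrong, and attrition allowances for the definitive trial could be set too optimistically.

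**Working it through.** **Inputs** (Sample size section): p = 0.75; 95% confidence, taken as two-sided because no side is stated; margin d = 0.05; lower bound 0.70; stated n = 75; recruitment target 76.

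**Reproducing the stated 75.** The standard formula is n = z² p(1 − p) / d².

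- With z = 1.96: 3.8415 × 0.1875 / 0.0025 = 288.1, so 289 patients.
- With z = 1: 0.1875 / 0.0025 = 75 exactly.

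The stated number is obtained only when the 95% multiplier is omitted, that is, when 0.05 is the standard error. The shortfall factor is 1.96² = 3.84.

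**Other readings of the same inputs** (n needed for a lower limit of 0.70 at p = 0.75):

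| Method | Two-sided 95% | One-sided 95% |
|---|---|---|
| Normal approximation (Wald) | 289 | 203 |
| Wald, continuity-corrected | 308 | 223 |
| Arcsine | 306 | 216 |
| Wilson | 323 | 228 |
| Exact (Clopper-Pearson) | about 335 | about 243 |

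None is near 75. A finite-population correction would give 75 only for a source population of about 101, which the protocol does not mention. A margin of 0.10 would need 73, close to 75, but that contradicts both the printed 0.05 and the printed 0.70.

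**Precision actually achieved at a rate of 75%.** Wald half-width = 1.96 × √(0.1875 / n).

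- n = 75: 1.96 × 0.0500 = 0.098; interval 0.652 to 0.848.
- n = 76: 1.96 × 0.0497 = 0.097; interval 0.653 to 0.847. For 57/76, Wilson gives 0.642 to 0.834 and exact gives 0.637 to 0.842.
- An interval of ±0.05 at n = 75 is ±1 standard error, which has about 68% confidence.

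**Rate that would have to be observed for a lower limit of 0.70 with n = 76.** By Wilson, 61/76 gives 0.6996, just short, and 62/76 (82%) gives 0.714. By Wald, 61/76 (80%) is enough. An observed 75% is not enough by either method.

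**If recruitment only just meets its progression criterion.** 0.70 × 76 = 53.2, so 54 patients. The Wald half-width is 1.96 × √(0.1875 / 54) = 0.115, with an interval of 0.635 to 0.865.

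**Which rate is meant.** The paragraph speaks of adherence and then of completion. If the rate were measured only in those still followed up at 75% retention, the denominator would be 0.75 × 76 = 57 and the half-width 1.96 × √(0.1875 / 57) = 0.112.

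**The case against.** The arithmetic cannot be defended, but the consequences can be argued down.

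- **The size is called pragmatic, and recruitment capacity supports it.** Two per month per centre, three centres and a 13-month window give 2 × 3 × 13 = 78, so 76 is plausible without any precision argument. This stands, and it is why the number need not change. It does not make a printed precision claim true.
- **No decision rule uses the 0.70 bound or the 0.05 margin.** The progression criteria are simple percentages, and the observed intervals will be reported at their true width. This also stands. The error misstates the precision expected in advance; it does not corrupt the final estimates.
- **Passing the recruitment criterion at 54 does not contradict a requirement of 75.** A threshold for progressing may sit below the recruitment target. This is fair. The figure for 54 only shows how much wider the interval becomes if recruitment stops near that threshold.
- **The omitted multiplier is an inference.** It is, although the match at 75 is exact. The inconsistency does not depend on how it arose.

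**Conclusion.** The statement is wrong as written and must be corrected. Seventy-five patients do not give a 95% interval of ±0.05 with a lower bound of 0.70 around a 75% rate; that needs 289 by the normal approximation, and more than 200 under every standard variant tried, including one-sided. The precision available is about ±0.10, with a lower limit between 0.64 and 0.65 depending on the method, so the interval is about twice as wide as claimed. At an observed 75% the trial cannot exclude a true rate of 70%, or of 66%.

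This rests on the plan's own 75% rate, on independent participants, and on all randomised participants forming the denominator. A smaller denominator makes the precision worse.

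**What to change.** Keep 76 participants and replace the precision sentence in the Sample size section with one based on a single named method, for example:

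*With 76 participants and a completion rate of 75%, the two-sided 95% CI (normal approximation) is 0.65 to 0.85, a half-width of about 0.10. If only 54 participants are recruited, the half-width is about 0.12.*

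If the Wilson method is to be used for reporting, quote 0.64 to 0.83 for 76 participants and recompute the figure for 54 by the same method.

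Delete the 0.05 margin, the 0.70 lower bound and the statement that at least 75 are required on that basis. Rest the choice of 76 on the pragmatic and recruitment grounds already given. Use one term for the rate (adherence, completion or retention) and state its denominator.

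The cost is wording only: no extra patients and no change to the analysis. The stated precision becomes less favourable. Keeping the ±0.05 claim instead would mean planning for about 289 patients, which is not warranted for a feasibility trial.

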### Adverse events

Adverse events (AEs) are, according to the definitions, any unfavourable or unintended event affecting patients in the study. In cases of prolongation of hospitalisation, death or significant clinical sequelae, these events are defined as serious AEs (SAEs), the occurrence of which will be informed to the study sponsor and the TSC at short notice. During protocol treatment, all deaths, all SAEs that are life-threatening and any unexpected SAE must be reported to the chief investigator using the SAE form within 48 hours of the initial observation of the event. In this trial, only those non-serious AEs associated with the lower limb, foot and mobility need to be reported. Safety aspects of the study will be monitored by the TSC, which will receive unblinded data for its judgement.

To standardise and optimise implementation of the intervention, and to further ensure the safety and well-being of research participants, all participants will be provided with standardised information on footwear and insole usage, how to increase wear time of the insoles, foot self-inspection and what to do in the event of a ‘foot attack’. This information will be reiterated at each appointment by the treating podiatrist. Participants will be advised to contact the treating podiatrist should any problems occur, in order that they can advise remanagement of these issues.

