### Study procedures

An overview of the study procedures are outlined in table 2. All participants will be invited to attend the baseline visit and three further study appointments at 3 months, 6 months and 12 months postrandomisation. Data at all time points will be collected in case report forms (CRFs) by the trial team. All data will be entered into a secure database by the Peninsula Clinical Trials Unit.

**Table 2 T2:** Study procedures for the Insoles to Ease Pressure (INSTEP) Study

Procedure	Baseline clinic (visit 1)	3 months* follow-up clinic (visit 2)	4 months qualitative follow-up*	6 months* follow-up clinic (visit 3)	12 months* follow-up clinic (visit 4)
Confirmation of eligibility	X				
Informed consent	X				
Demographics and history	X				
Plantar pressure in-shoe recording	X	X		X	X
Randomisation	X				
Intervention provision (including plantar pressure recording)	X				
Outcome measures (ulcer incidence; photographs, activity and self-care questionnaires)	X	X		X	X
Semistructured interviews (in participants’ homes)			X		
Journal entries		X		X	X
Serious adverse event recording		X	X	X	X

*Postrandomisation.

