### Statistical analysis plan

A comprehensive statistical analysis plan (SAP) will be drafted prior to the final database lock; the SAP will be agreed with the trial steering committee (TSC) in the absence of a data monitoring committee. An extended CONSORT^18^ flow chart will be used to present descriptive data on screening, enrolment, intervention allocation, follow-up and assessment. It will also show any deviations from protocol, for example, participants receiving an ‘incorrect’ treatment. Descriptive data will be presented by the intervention group on baseline characteristics, for example, age, sex, type of diabetes.

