### Ethical issues

The protocol, V.1.0 (12/7/2017), was reviewed by the South-West Exeter Research Ethics Committee (REC) and was given a favourable opinion (REC ref 17/SW/0169) on 18 September 2017. Health Research Authority regulatory approval was given on 19 September 2017 and the study was adopted on the NIHR portfolio on 15 August 2017. Plymouth University is the sponsor of the study. The study will comply with the International Conference for Harmonisation of Good Clinical Practice guidelines and the UK Framework for Health and Social Care Research

Amendments to the protocol or study documents will be submitted to the REC and can only be implemented once approval has been obtained. Amendments will be tracked in the protocol and the version of the protocol will be updated.

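### The SAE definition counts prolonged hospitalisation but not a new admission, and leaves out the life-threatening events on which its own 48-hour rule relies

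*Protocol article*

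**What the plan says.** The Adverse events section of the protocol article sets out a definition and three rules.

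- **Definition of serious:** "In cases of prolongation of hospitalisation, death or significant clinical sequelae, these events are defined as serious AEs (SAEs". 
- **Short-notice route:** for SAEs so defined, "the occurrence of which will be informed to the study sponsor and the TSC at short notice".
- **48-hour rule:** "all deaths, all SAEs that are life-threatening and any unexpected SAE must be reported to the chief investigator", on the SAE form, within 48 hours of first observation.
- **Non-serious events:** "only those non-serious AEs associated with the lower limb, foot and mobility need to be reported".

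On oversight, the same section states: "Safety aspects of the study will be monitored by the TSC, which will receive unblinded data for its judgement". The Statistical analysis plan section says that the SAP will be agreed with the TSC "in the absence of a data monitoring committee".

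Table 2 (Study procedures) has one safety row, "Serious adverse event recording", marked at 3, 4, 6 and 12 months. A separate outcome row in that table schedules ulcer incidence and photographs at baseline, 3, 6 and 12 months.

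The Ethical issues section adds a general commitment: "The study will comply with the International Conference for Harmonisation of Good Clinical Practice guidelines".

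**The concern.** Two things in the definition do not fit. It treats the lengthening of a hospital stay as serious and is silent on the admission itself. It also omits life-threatening events, which the 48-hour rule then names as a kind of SAE.

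The definition decides which events are reported and how fast. An event that falls outside it is non-serious, and the non-serious rule is restricted to three body or function areas. A gap in the definition can therefore become a gap in reporting. With no data monitoring committee, what the TSC sees is the whole of the safety oversight that the article describes. Centres that fill the gap differently would also report differently, which makes the safety data less comparable across the three sites.

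**Working it through.** No arithmetic applies, and the article gives no figure to reproduce. The check is to read the Adverse events section as a decision rule and pass typical events through it.

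**The rule, in order**

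1. Did the event prolong a hospital stay, cause death or leave significant clinical sequelae? If yes, it is an SAE and the sponsor and TSC are told at short notice.
2. If no, it is non-serious. Is it associated with the lower limb, foot or mobility? If yes, it is reportable as a non-serious AE.
3. If no again, it need not be reported.

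**Events passed through the rule**

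| Event | Step 1 | Step 2 | Result as written |
|---|---|---|---|
| A. New admission unrelated to limb, foot or mobility; survived, stay not prolonged, no significant sequelae | No | No | Need not be reported |
| B. As A, but the stay is prolonged | Yes | – | SAE; sponsor and TSC told at short notice |
| C. New admission for a foot infection or a fall; survived, stay not prolonged, no significant sequelae | No | Yes | Reportable, but as non-serious |
| D. Life-threatening event outside those areas; full recovery, no prolonged stay | No, on the literal list | No | Depends on the reading (below) |
| E. Death | Yes | – | SAE and 48-hour rule |

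**A against B.** The two differ only in whether the stay was extended. One goes to the sponsor and TSC at short notice and the other need not be reported.

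**C.** The event is still captured, but it misses the short-notice route, and the section gives no recipient or time limit for non-serious events. Falls are relevant here: the footnote to Table 1 gives them as an example of the health deterioration that the exclusion criteria are meant to avoid.

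**D.** The 48-hour sentence can be read in two ways. If life-threatening events are understood to be serious in their own right, D is reported within 48 hours, and the definition has simply left that criterion out. If the sentence selects the life-threatening ones among events already serious on one of the three listed grounds, D is not reached. The text does not settle which is meant.

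**Is the list widened elsewhere?** No other section of the article gives seriousness criteria. The good clinical practice sentence under Ethical issues lists none and does not refer to the definition.

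**Table 2.** The reportable non-serious events are the lower-limb, foot and mobility ones. Plantar ulceration is among them and already has a scheduled assessment as an outcome. The rest, such as falls or other limb problems, have no row.

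**The case against.** The strongest reply is that this is a condensed article. The section introduces its definition of AEs by reference to definitions, the Ethical issues section names a full protocol (V.1.0) that is not shown, and the study commits itself to good clinical practice. Sites may well work from a complete list. The sentence also contains no word such as only, so it does not declare itself exhaustive. This makes it less likely that sites would apply the gap in practice. It does not remove the point, because the article did not leave the definition to another document. It states one, beside rules that do not match it.

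Several stronger readings are tempting, and the article does not support them.

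- **That the definition and the 48-hour rule contradict each other, so that a survived life-threatening event never reaches the TSC.** The more natural reading of the 48-hour sentence is that such events are serious. The omission is a mismatch, not a strict contradiction.
- **That every admission unrelated to the foot goes unreported.** Admissions related to the lower limb or mobility remain reportable, as do those with death, a prolonged stay or significant sequelae. The term for sequelae is undefined and may catch others. The non-serious rule also sets a minimum and does not bar a site from reporting more.
- **That reportable foot events have no collection point.** Table 2 is offered as an overview and already schedules ulcer assessment. Participants are also told to contact the treating podiatrist with any problem. What is missing is a table row for the remaining events, not a process.
- **That SAE rates by arm, and those carried to the definitive trial, are understated.** The article plans no such analysis. SAE rates are not among its listed outcomes, and the progression criteria concern recruitment, retention and completion.

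**Conclusion.** The point holds in a limited form. The definition is incomplete against the section's own reporting rules. As written, it lets a first admission outside the limb, foot and mobility areas, without death, prolonged stay or significant sequelae, go unreported. It also places a comparable foot- or fall-related admission outside the short-notice route to the sponsor and TSC.

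The size cannot be computed. The population at risk is the 76 planned participants over 12 months, but the article gives no admission or life-threatening event rate from which to estimate a count. The consequence lies in the completeness, timing and comparability of the safety information that the TSC receives. It does not reach any feasibility estimate, progression criterion or sample size figure.

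The conclusion assumes that the sentence in the article is the definition sites apply, and that significant clinical sequelae does not itself cover an uncomplicated admission. If the full protocol carries a wider list, the error is confined to the article's wording. The correction is worth making in either case.

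**What to change.** Reconcile the definition with the reporting rules in the Adverse events section:

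- add hospital admission, and not only its prolongation, to the seriousness criteria;
- add life-threatening events to the same list, so that the 48-hour rule refers to a class that the definition contains.

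As a minor alignment, have Table 2 show the recording of reportable non-serious lower-limb, foot and mobility AEs other than ulcers, which are already collected as an outcome.

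If the full protocol already holds these criteria, only the article's wording needs correcting. Otherwise the cost is a wording change to the protocol and case report form, submitted to the ethics committee as the Ethical issues section requires for any amendment, and a few more SAE forms. No visit, analysis or recruitment target changes.

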### Ethical issues

The protocol, V.1.0 (12/7/2017), was reviewed by the South-West Exeter Research Ethics Committee (REC) and was given a favourable opinion (REC ref 17/SW/0169) on 18 September 2017. Health Research Authority regulatory approval was given on 19 September 2017 and the study was adopted on the NIHR portfolio on 15 August 2017. Plymouth University is the sponsor of the study. The study will comply with the International Conference for Harmonisation of Good Clinical Practice guidelines and the UK Framework for Health and Social Care Research

Amendments to the protocol or study documents will be submitted to the REC and can only be implemented once approval has been obtained. Amendments will be tracked in the protocol and the version of the protocol will be updated.

